## Other Outcomes of Interest

Basic demographic measures concerning each patient as well as a number of other measures that will serve as covariates in the analysis, such as patients’ health status, memory ability, state anxiety, state depression, and medical knowledge. The rationale for including these measures is that they are potential moderators of participants’ recall of discharge information and thus should be included in the statistical analysis.

## Safety Outcomes

NA

# STUDY DESIGN

## General study design and justification of design

The study will use a cluster randomized controlled trial. Clusters of physicians (cohorts of six physicians commencing training in a three-month period; total of four clusters in the one-year intervention period) will be assigned to one of two types of training (information-structuring skills vs. emotion-handling skills). The physicians won’t know to which cluster they belong. The primary outcome of the study will be patients’ recall of information as a function of physicians’ training. For this purpose, we aim to recruit 50 patients presenting to the emergency department with chest pain and 50 patients with abdominal pain in each three-month period (*N* = 400, in the one-year study period) and document the respective discharge communication (via audio recordings). In addition, each patient will be asked to recall the discharge information immediately after the discharge event, seven days and 30 days later (telephone interview), as well as complete a number of other measures to assess secondary outcomes, such as overall satisfaction and adherence to recommendations. The study will be conducted at the emergency department of the University Hospital of Basel (Switzerland).

## Methods of minimising bias

### Randomisation

Clusters of physicians will be pseudo-randomly assigned to one of the two training programs (information structuring vs. emotion-handling skills training).

Table 3. Training/Interviewing Timeline for Each Cluster of Physicians (*k*)/Patients (*n*)

| Cluster | Months 1-3 | Months 4-6 | Months 7-9 | Months 10-12 |
| --- | --- | --- | --- | --- |
| 1 | Information Structuring  (*k*=6, *n* = 100) |  |  |  |
| 2 |  | Emotion Skills  (*k*=6, *n* = 100) |  |  |
| 3 |  |  | Information Structuring  (*k*=6, *n* = 100) |  |
| 4 |  |  |  | Emotion Skills  (*k*=6, *n* = 100) |

### Blinding procedures

Physicians at the University Hospital Basel will receive a communication skills training (information structuring or emotional skills training) without knowing about the other training and are therefore blinded.

### Other methods of minimising bias

The two trainings will follow the same structure, with physicians receiving the same intensity of teaching. Both programs will consist of one four-hour session of training with an experienced communication expert ([name] [name]). Also, both training programs will consist of theory and practice components as well as a test session to assess the actual use of communication skills (see Table 4).

Table 4. Outline of Physician’s Information Structuring and Emotion Skills Training

| Training | Module | Description |
| --- | --- | --- |
| Information Structuring | Theory (1h) | 1. Rationale for communication training  2. Rationale for information structuring training  3. Introduction to InFARCt scheme |
|  | Practice (3h) | 1. Instructor example 2. Practice in dyads 3. Overall feedback |
|  | Test (5 min per trainee) | 4. Vignette plus information delivery |
| Emotion Skills | Theory (1h) | 1. Rationale for communication training  2. Rationale for emotion skills training  3. Introduction to NURSE scheme |
|  | Practice (3h) | 1. Instructor example 2. Practice in dyads 3. Overall feedback |
|  | Test (5 min per trainee) | 4. Vignette plus information delivery |

## Unblinding Procedures (Code break)

We will not need unblinding. The physicians and experimenters will have full knowledge of the treatment underway and patients will be blind to the condition throughout. Only the data analysis/transcription of discharge and phone interviews will be done in a blind fashion because participants will receive some code (e.g., random alphanumeric code) to prevent identification by the researcher.

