## Recruitment and screening

All physicians participating in the study will be asked to contact a member of the study team about any pending discharge communication with a patient suffering from chest pain or a patient suffering from abdominal pain. Eligible participants (see 7.1) will be asked to give written consent to participate in the study. There will be no monetary compensation for the participation.

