## Assessments of outcomes

The pre-discharge assessment will take about 15 minutes and aims to collect basic demographic measures concerning each patient as well as a number of other measures that will serve as covariates in the analysis, such as patients’ health status, memory ability, state anxiety, state depression, and medical knowledge. The rationale for including these measures is that they are potential moderators of participants’ recall of discharge information and thus should be included in the statistical analysis.

Immediately after the discharge communication event, patients will be interviewed for up to five minutes to assess recall of information provided during the discharge consultation and to assess patients’ satisfaction with the encounter.

Finally, two brief interviews of 5–10 minutes will be conducted over the phone seven days after discharge and 30 days after discharge to retest recall of discharge information, thus assessing the reliability of the main outcome measure and the time component of recall. In addition, patients will be asked about self-reported adherence to discharge recommendations, and overall assessment of the discharge consultation. Table 5 provides a description of the measures collected in each phase. Patients will also be asked about information provided by their General Practitioners to control for possible confounds of receiving extra or additional information from a third-party.

Table 5. List of Measures Used in Patient Interviews and Respective Description

| Phase | Measure | Description |
| --- | --- | --- |
| Pre-discharge  Assessment | Demographics | Age, Sex, Education, Marital Status, Nationality |
|  | Health-related quality of life | German version of the SF-12,^29^ a generic, short-form health survey with 12 items developed to provide a valid and reliable method to monitor subjective aspects of health and quality of life. |
|  | Memory | CERAD Word List Memory test, a free recall memory  test that assesses learning ability for new verbal information.^30^ A ten-item word list is presented over three trials (at the rate of 1 every 2 seconds) with a different word order each trial. The participant is instructed to read each word aloud as it is presented and then asked to recall as many words as possible. |

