|  | State anxiety and depression | German version of the Hospital Anxiety and Depression Scale (HADS-D),^31^ a brief instrument containing two scales of 7 items assessing state anxiety and depression. |
|  | Medical knowledge | Multiple-choice test consisting of 6 questions of increasing difficulty developed by our research team. |
| Interview | Immediate recall | Patients will be asked to freely recall all information provided immediately after the discharge event, “Can you tell me all the information your physician just provided?”, and repeated use of prompts, “Was there any other information you can recall?” until the patient cannot recall any more information. |
|  | Satisfaction | Once patients cannot recall any additional information, they will be asked to characterize their satisfaction with the discharge communication event and physician. Specifically, we will previously developed items (see Study 4) asking patients to rate on a scale from 1 to 10 the (1) physician’s comprehensibleness, (2) information structuring, and (3) willingness to recommend the physician to family and friends. |
| Telephone Interview | Delayed recall | Patients will be asked to freely recall all information mentioned in the discharge event, “Can you tell me all the information your physician provided when you left the emergency department?”, and repeated use of prompts, “Was there any other information you can recall?” until the patient cannot recall any more information. In addition, patients will be asked whether they have received additional information from their general practitioner since discharge. |
|  | Adherence to recommendations | Patients will be asked to list all the physician recommendations that they have actively pursed, “Can you tell me which of your physician’s recommendations you have pursued?”. |
|  | Overall assessment | German version of the Patient Reactions Assessment (PRA-D),^32^ composed of three 5-item scales designed to measure information, affective, and communication components of physician–patient communication. |

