### Assessment of primary outcome

The primary outcome of the study will be patients’ recall of information as a function of physicians’ training. For detailed assessment see Table 5.

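### The protocol calls physicians blinded in two sections and unblinded in a third, and primary recall appears to be elicited by unmasked staff with no fixed rule for when prompting stops

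*Protocol*

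**What the plan says.** **Physicians.** Protocol section 6.1 says: "The physicians won’t know to which cluster they belong". Section 6.2.2 says that physicians receive their training "without knowing about the other training and are therefore blinded". Section 6.3 says: "The physicians and experimenters will have full knowledge of the treatment underway and patients will be blind to the condition throughout".

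**What is masked.** Section 6.3 continues: "Only the data analysis/transcription of discharge and phone interviews will be done in a blind fashion". The means is a random code in place of the participant's identity.

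**Primary outcome.** Section 9.2.1: "The primary outcome of the study will be patients’ recall of information as a function of physicians’ training". Table 5 in section 9.2 gives an opening question and one neutral follow-up prompt, which is repeated "until the patient cannot recall any more information". Sections 9.1 and 9.2 give a duration: "patients will be interviewed for up to five minutes to assess recall of information provided during the discharge consultation". That time also covers satisfaction. The telephone interviews last 5 to 10 minutes. The synopsis says that the discharge encounter and all interviews are audio-recorded.

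**Allocation and referral.** Table 3 in section 6.2.1 places each cohort in its own three-month period, with one arm per period. Section 7.3 draws the first training at random and alternates after that. Section 7.2: "All physicians participating in the study will be asked to contact a member of the study team about any pending discharge communication".

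**The concern.** The protocol claims a protection against bias in two places and withdraws it in a third. This matters because the primary outcome depends on how it is elicited. The number of items recalled can rise with persistence in prompting, and the persistence is left to the interviewer's judgement. An interviewer who knows the arm and the hypothesis may, without intending to, press longer in one arm. Masked transcription cannot undo that, because the extra items are already on the recording.

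Two further points add to the exposure:

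- The arm can be inferred from the calendar, so a random ID alone does not mask a scorer who sees dates or the physician.
- Patients reach the study through a physician who has already been trained. Assigning cohorts to arms does not protect against selective referral after assignment.

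**Working it through.** **Step 1: the blinding statements, role by role.**

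| Role | Sections 6.1 and 6.2.2 | Section 6.3 |
|---|---|---|
| Physicians | Do not know their cluster or the other training; called blinded | Full knowledge |
| Experimenters (term not defined) | Not mentioned | Full knowledge |
| Patients | Not mentioned | Blind |
| Transcription and analysis | Not mentioned | Blind, by coded ID |

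The physician row cannot stand as written. The mildest reading is that physicians know the training they received but not that another exists. That does not fit full knowledge, and it is not blinding to the intervention they deliver. It would also be hard to keep up. The study schedule has physicians staying about six months, with a new cohort every three, and the arms alternate. Cohorts with different trainings would therefore work side by side.

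**Step 2: who elicits recall.** Section 7.2 and the synopsis mention only members of the study team. No masked interviewer is named. That the experimenters of section 6.3 are the interviewers is an inference, though the obvious one.

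**Step 3: what is fixed in the interview.** The opening question, the prompt wording and a time range are fixed. The number of prompts and an observable stopping point are not. The written criterion is that the patient has no more to recall, and the interviewer must judge when that is so.

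**Step 4: masking of scorers.** Under Table 3, the date of discharge identifies the quarter, and the quarter identifies the arm. The physician identifies the cohort, and so the arm. The protocol does not say whether scorers see either. The discharge recording may also reveal which communication scheme was used.

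**Step 5: scale, under an assumed bias.** The protocol gives no figure for the size of a bias. The only recall means and SDs it reports are those of Study 4 (section 3.1). For first-year psychology students these are 8.1 (SD 4.3) structured and 5.7 (SD 3.7) unstructured.

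- Difference: 8.1 − 5.7 = 2.4 items.
- Pooled SD, assuming equal group sizes: √[(4.3² + 3.7²)/2] = √[(18.49 + 13.69)/2] = √16.09 = 4.01.
- Check: 2.4/4.01 = 0.60, which agrees with the stated Cohen's *d*.

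| Assumed difference between arms from prompting | In SD (÷ 4.01) | Share of 2.4 items |
|---|---|---|
| 0.25 item | 0.06 | 10% |
| 0.5 item | 0.12 | 21% |
| 1 item | 0.25 | 42% |

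**Step 6: what that could do to the test.** Assume no true effect, 200 patients per arm, SD 4.01 and a two-sided 5% level (the protocol states none).

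- Without clustering: SE = 4.01 × √(2/200) = 0.401. Biases of 0.25, 0.5 and 1 item give false-positive rates of 0.10, 0.24 and 0.70 (normal approximation).
- With 12 physicians per arm and an assumed physician ICC of 0.05: 200/12 = 16.7 patients per physician; design effect 1 + 15.7 × 0.05 = 1.78; SE = 4.01 × √(2 × 1.78/200) = 0.535. With 22 degrees of freedom the rates are 0.07, 0.15 and 0.43.

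These are illustrations. The second set leaves out any cohort-level variance.

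**The case against.** The strongest replies, and what stands of each:

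- **Prompting is not unlimited.** A reader might infer that it is, because no number is given. The documents do not support that: the immediate interview is limited to five minutes and the telephone interviews run 5 to 10. The prompt is scripted and neutral, and the same rule applies in both arms. This stands. However, a time ceiling does not equalise prompting below it.
- **The immediate interview may already be handled blind.** A reader might infer from section 6.3 that it is left out. Its phrase about discharge and phone interviews can be read as covering the interview at discharge, and that may be the more natural reading. The wording is ambiguous, not a demonstrated gap. Blind handling afterwards would still not reach elicitation.
- **Selection has no clear direction.** If section 6.2.2 is right, physicians have no comparison in mind. They are asked to report any pending discharge of an eligible patient, and memory, anxiety, depression, medical knowledge and health status are measured before discharge as covariates. This weakens the selection argument. Covariates mitigate only what they measure.
- **The scale does not transfer cleanly.** Study 4 was five-minute written recall of a 28-item video by students. This stands, so the figures show order of magnitude only.
- **Recordings allow an audit.** They do, but an audit finds differential prompting after the event and cannot repair it.

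**Conclusion.** The contradiction between sections 6.1 and 6.2.2 on one side and 6.3 on the other is plain in the text and needs correcting. As section 6.3 stands, the primary outcome is open to differential elicitation by staff who appear to be unmasked, with a lesser risk from referral after allocation. This is a risk of bias; the documents do not show that bias will occur, or its direction.

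The size is unknown. If prompting differed between arms by 0.25 to 1 item, which is purely an assumption, the distortion would be about 0.06 to 0.25 SD on Study 4's psychology-student scale, or 10% to 42% of that subgroup's 2.4-item difference. The conclusion rests on two inferences: that the experimenters include the interviewers, and that scorers may see dates or physician. If the sponsor can show otherwise, the blinding wording still has to be reconciled. The point should be settled before recruitment, because neither prompting nor referral can be corrected afterwards.

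**What to change.** 1. Replace the statements in sections 6.1, 6.2.2 and 6.3 with one role-by-role account covering physicians, interviewers, patients, transcribers, scorers and analysts. It should not claim that physicians are blinded to the training they deliver.
2. Do not tell interviewers which program the current cohort received.
3. Keep the scripted neutral prompt and add an explicit stopping rule, identical for every patient and every interview. For example, stop after the first prompt that yields no new item.
4. State that all recall recordings, expressly including the immediate interview, are scored with physician, date and sequence removed, by a coder who has not heard that patient's discharge recording.

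**Cost.** Protocol and script wording, and slightly more preparation of recordings that are already planned. Some interviewers may still guess the arm, since a whole quarter belongs to one program.

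Two stronger remedies are not needed for this point. A fixed cap on the number of prompts would truncate recall and could weaken a true effect. Replacing physician referral with screening from a patient list may need staff that the protocol does not provide for.

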| **Measurements and Procedures:** | Study Procedure  The study involves two components: (a) the intervention component, consisting of the two physician-training programs and (b) the evaluation component, consisting of an assessment of the interventions through patient testing and interviews.  Physician Training  Physicians will be recruited to participate in the study, which will serve as a complement to physicians’ regular emergency department training. The two programs will follow the same structure, with physicians receiving the same intensity of teaching. Both programs will consist of one four-hour session of training with an experienced communication expert ([name] [name]). Also, both training programs will consist of theory and practice components as well as a test session to assess the actual use of communication skills. The information-structuring program will include a review of scientific evidence on the superiority of structured over non-structured communication as well as hands-on practical exercises in dyads to train structured communication skills. Specifically, participants will be introduced to the ‘InFARcT-scheme’ (categorization scheme that could, in principle, help physicians to structure information; for more information see: past work by research team) and trained to use it to structure their communication. The emotion skills training program will follow a similar structure but will focus on the NURSE communication model.^28^ The NURSE model encourages caretakers to engage in naming, understanding, respecting, supporting, and exploring patients’ emotional reactions with the goal of reducing anxiety and increasing compliance. In addition, physicians in both conditions will receive a one-hour booster session two weeks after the initial training involving a discussion of patient examples to whom they had applied the newly acquired skills. The rationale for the use of a booster session is to ensure that communication goals are maintained as a high priority and that physicians have a chance to receive additional feedback early in their training.  Patient Interviews  All physicians participating in the study will be asked to contact a member of the study team about any pending discharge communication with a patient suffering from chest pain or a patient suffering from abdominal pain. Eligible participants (see section on Participants) will be asked to give written consent to participate in the study and complete a pre-discharge assessment. The pre-discharge assessment will take about 15 minutes and aims to collect basic demographic measures concerning each patient as well as a number of other measures that will serve as covariates in the analysis, such as patients’ health status, memory ability, state anxiety, state depression, and medical knowledge. The rationale for including these measures is that they are potential moderators of participants’ recall of discharge information and thus should be included in the statistical analysis.  Immediately after the discharge communication event, patients will be interviewed for up to five minutes to assess recall of information provided during the discharge consultation and to assess patients’ satisfaction with the encounter.  Finally, two brief interviews of 5–10 minutes will be conducted over the phone seven days after discharge and 30 days after discharge to retest recall of discharge information, thus assessing the reliability of the main outcome measure and the time component of recall. In addition, patients will be asked about self-reported adherence to discharge recommendations, and overall assessment of the discharge consultation. Table 4 provides a description of the measures collected in each phase. Patients will also be asked about information provided by their General Practitioners to control for possible confounds of receiving extra or additional information from a third-party.  The discharge communication encounter as well as all interviews will be recorded with audio recording devices. |

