## Investigational Product (treatment, device) and Indication

**Physician Training**

Physicians will be recruited to participate in the study, which will serve as a complement to physicians’ regular emergency department training. The two programs will follow the same structure, with physicians receiving the same intensity of teaching. Both programs will consist of one four-hour session of training with an experienced communication expert ([name] [name]). Also, both training programs will consist of theory and practice components as well as a test session to assess the actual use of communication skills. The information-structuring program will include a review of scientific evidence on the superiority of structured over non-structured communication as well as hands-on practical exercises in dyads to train structured communication skills. Specifically, participants will be introduced to the InFARcT-scheme and trained to use it to structure their communication. The emotion skills training program will follow a similar structure but will focus on the NURSE communication model.^28^ The NURSE model encourages caretakers to engage in **n**aming, **u**nderstanding, **r**especting, **s**upporting, and **e**xploring patients’ emotional reactions with the goal of reducing anxiety and increasing compliance. In addition, physicians in both conditions will receive a one-hour booster session two weeks after the initial training involving a discussion of patient examples to whom they had applied the newly acquired skills. The rationale for the use of a booster session is to ensure that communication goals are maintained as a high priority and that physicians have a chance to receive additional feedback early in their training.

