### Primary Analysis

The primary analysis will evaluate the effects of the two trainings. This evaluation will be done in January/February 2016 after data collection is done. A doctoral student and the PI will do the data analysis.

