### Case Report Forms

Data is recorded with electronic Case Report Forms (e-CRF). For each enrolled study participant, a CRF is maintained. CRFs will be kept current to reflect subject status at each phase during the course of study. Participants will not be identified in the CRF by name or initials and birth date. An appropriate coded identification, in our case a participant number, will be used. Only the principal investigator [name], or the investigators [name] and [name] will be authorized to make CRF entries. Every authorised person can be identified by his or her own login.

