### Specification of source documents

Source data will be available at the site to document the existence of the study participants. Source data will include the original documents relating to the study, as well as the medical treatment and medical history of the participant. The source document will consist of demographic data, date of discharge communication and date of follow ups, participation in study and Informed Consent Forms, randomisation number. Source data are found at the site.

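### Section 6.3 rests blind transcription and analysis on a patient code, which does not mask the training arm, so blinding of recall scoring and analysis is not secured

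*Protocol*

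**What the plan says.** Section 6.3 says that physicians and experimenters know the treatment and that patients do not. For the later steps it says: "Only the data analysis/transcription of discharge and phone interviews will be done in a blind fashion because participants will receive some code". It describes the code as "e.g., random alphanumeric code) to prevent identification by the researcher". No other masking device is given for these steps.

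Other sections bear on whether such a code can work:

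- The synopsis (Measurements and Procedures) states: "The discharge communication encounter as well as all interviews will be recorded with audio recording devices".
- Section 3.2 says of the experimental programme that "participants will be introduced to the InFARcT-scheme and trained to use it to structure their communication". The control programme teaches the NURSE model of responding to emotions.
- Section 6.2.1, Table 3 ("Training/Interviewing Timeline for Each Cluster of Physicians") gives each three-month block a single training. Section 7.3 draws the first training at random and alternates after that.
- Section 12.1.2 lists among the source data the "date of discharge communication and date of follow ups".
- Section 11.4.2 says: "A doctoral student and the PI will do the data analysis". Section 12.1.1 names the principal investigator among the few who "will be authorized to make CRF entries".
- Section 9.2, Table 5 defines recall as free oral recall, prompted until the patient has nothing more to add.

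**The concern.** The reason that section 6.3 gives does not lead to its conclusion. Replacing a name by a random code protects identity. Blinding of outcome scoring needs the arm to be hidden, and the arm here belongs to the physician's cohort and the calendar quarter, not to the patient's name.

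This matters because the primary outcome depends on human judgement. Free recall becomes a score only when someone decides which statements count as a recalled fact. Borderline statements leave room for leniency, and a scorer who knows the arm can apply it unevenly without noticing. The interviewers are openly unblinded, so among the steps after the interview, transcription and analysis are where 6.3 places its protection. If the code does not mask the arm, a report that describes these steps as blind would claim more than the plan has secured.

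**Working it through.** There is no stated figure to reproduce, so the check is mainly a comparison of sections.

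**Step 1: what the code hides.** By its own description in 6.3 it prevents identification of participants. Arm, cohort, physician and date are not mentioned.

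**Step 2: does the recorded content show the arm?** Section 6.3 includes the discharge recordings in the material to be handled blind. The programmes aim to make those conversations differ: ordered by the InFARcT categories in one arm, NURSE-style in the other (3.2). The better the training works, the easier the arm is to recognise. This applies to the discharge recording. A recall interview heard alone and without a date need not reveal the arm.

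**Step 3: does the calendar show the arm?**

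| Months | Training (Table 3) | Planned patients |
|---|---|---|
| 1-3 | Information structuring | 100 |
| 4-6 | Emotion skills | 100 |
| 7-9 | Information structuring | 100 |
| 10-12 | Emotion skills | 100 |

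As tabulated, the block identifies the arm for 4 × 100 = 400 of 400 patients. Strict alternation (7.3) allows only two sequences, so anyone who knows the arm of one block knows all four. Discharge and follow-up dates are kept (12.1.2), and the protocol states no step that removes them from the material to be scored or analysed.

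**Step 4: who handles the data?** The principal investigator is one of two analysts (11.4.2) and may make CRF entries (12.1.1). That is a possible route to the arm, not proof that it is used. The model in 11.4 nests physicians within training programme, so the analyst needs a training variable. The protocol does not say that its labels are masked.

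**Step 5: scale, as illustration only.** The protocol gives no figure for uneven scoring, so the shifts below are assumptions. Inputs: the smallest and largest standard deviations of recall in Study 4 (section 3.1), 3.7 and 5.1 items; 200 patients per arm; no true effect; two-sided 5% test; no clustering.

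- d = shift / SD
- standard error of d = √(2/200) = 0.10
- rejection rate = Φ(d/0.10 − 1.96) + Φ(−d/0.10 − 1.96)

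| Assumed shift (items) | d at SD 5.1 | d at SD 3.7 | Rejection rate |
|---|---|---|---|
| 0.25 | 0.049 | 0.068 | 7.8% to 10.4% |
| 0.5 | 0.098 | 0.135 | 16.5% to 27.2% |

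These standard deviations come from students writing down the content of a 28-item video, not from patients recalling aloud. With clustering, the standard error would be larger and a given shift would raise the rejection rate less. The table shows that a small uneven credit would not be harmless; it does not estimate what would happen.

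**The case against.** A reader might infer something stronger: that recall scoring and analysis will in fact be unblinded, and that the report would claim blinding that never existed. The protocol does not support this.

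- **The scorer is not described.** The protocol does not name the recall scorer, or say that this person hears discharge recordings, sees dates or works in recruitment order. Dates are source data at the site; nothing says they travel with transcripts. A random code, if used as in the example, also hides recruitment order.
- **The calendar mapping is planned, not certain.** Physicians stay six months while a new cohort starts every three (Study schedule), and all participating physicians are asked to refer patients (7.2). A first-cohort physician's patient in months 4-6 is not expressly excluded, although Table 3 plans none.
- **Content is a clue, not proof.** In Study 3, before any training, diagnosis and follow-up were covered in 100% of conversations and treatment in 75%. Hearing these topics does not identify the arm. Their order and the style may, but how reliably is unknown.
- **Entry rights show little.** Permission to enter CRF data does not mean that the principal investigator enters them, scores recall or sees the arm.
- **Other blinding is claimed.** Patients are described as blind in 6.3, and 6.2.2 calls physicians blinded because they do not know of the other training. Transcription and analysis are thus not the only steps presented as blind.

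These points stand, and they limit the conclusion. It can also be said that separation of scorers, scoring order and score lock belong in an analysis plan or coding manual that is not shown. That answers a complaint about missing detail. It does not answer this one: 6.3 names a mechanism and gives it as the reason for blindness, and that mechanism cannot do the work.

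**Conclusion.** The point holds in this form: the patient code in 6.3 does not mask the arm, so it does not secure blind recall scoring or blind analysis. For transcription of discharge recordings the promise is weakest, because the intervention is meant to be audible there. For recall scoring and analysis, the protocol neither establishes blinding nor shows that it would fail.

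The only firm size is the calendar result: the planned block identifies the arm for all 400 patients, provided recruitment follows Table 3. The size and direction of any scoring bias are unknown. The illustrative shifts of 0.25 to 0.5 items correspond to about 0.05 to 0.14 standard deviations, but they are assumptions. They should not be read as a known share of the planned effect, for which the protocol itself gives two values (.4 in section 11.2, .59 in the synopsis). The change is worth making because the primary outcome is judged by people and the remedy is modest.

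**What to change.** Rewrite section 6.3 as follows.

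1. State that transcription of the discharge recordings is not blind.
2. Have one existing team member draw up, from each discharge recording, a neutral and unordered list of the facts given, without category headings. Another member, who has not heard that patient's discharge recording, scores the recall transcripts against it.
3. Remove dates and sequence from the material to be scored, and score in random order within batches that mix both trainings, for example quarters 1 and 2 together, then 3 and 4.
4. Lock the recall scores before the training code is merged.
5. Give the analysts masked arm labels (A and B) until the primary model has been run. The extract must also omit calendar dates, or Table 3 undoes the mask.

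**Cost.** Scoring waits until a mixed batch is available, and tasks must be divided within the existing team. There is no added burden for patients. With three recall interviews per patient, each batch holds up to 200 × 3 = 600 interviews. Scoring in two batches rather than one at the end lets half the work proceed earlier, which helps to keep the January/February 2016 analysis. Follow-up recall from late in the last quarter will still arrive close to that date.

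**What remains.** The person who lists the facts is not blind, and a patient's recall may itself follow the taught order. The change reduces the risk; it does not remove it, and 6.3 should say so.
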